# Photodynamic therapy with *Bixa orellana* extract and LED for the reduction of halitosis: study protocol for a randomized, microbiological and clinical trial

**DOI:** 10.1186/s13063-018-2913-z

**Published:** 2018-10-29

**Keywords:** Halitosis, Photodynamic therapy, *Bixa orellana*

## Abstract

**Background:**

Halitosis is an unpleasant breath odour that can interfere with the professional life, social life and quality of life of people who suffer from it. A modality of treatment that has been increasing in dentistry is antimicrobial photodynamic therapy (aPDT). *Bixa orellana*, popularly known as “urucum” is a plant native to Brazil. The seeds are used to produce a dye that is largely used in the food, textile, paint and cosmetic industries. The aim of this study is to verify whether aPDT with *Bixa orellana* extract and blue light-emitting diodes (LEDs) is effective in reducing halitosis. This method will also be compared with tongue scraping, the most commonly used conventional method for tongue coating removal, and the association of both methods will be evaluated.

**Methods/design:**

A randomized clinical trial will be conducted at the dental clinic of the Universidade Nove de Julho*.* Thirty-nine patients will be divided by block randomization into three groups (*n* = 13) according to the treatment to be performed. In Group 1, tongue scraping will be performed by the same operator in all patients for analysis of the immediate results. Patients will also be instructed on how to use the scraper at home. Group 2 will be treated with aPDT with *Bixa orellana* extract and the LED light curing device: Valo Cordless Ultradent®. Six points in the tongue dorsum with a distance of 1 cm between them will be irradiated. The apparatus will be pre-calibrated at wavelength 395–480 nm for 20 s and 9.6 J per point. In Group 3, patients will be submitted to the tongue scraping procedure, as well as to the previously explained aPDT. Oral air collection with the Oral Chroma™ and microbiological collections of the tongue coating shall be done before, immediately after and 7 days after treatment for comparison.

**Discussion:**

Halitosis treatment is a topic that still needs attention. The results of this trial could support decision-making by clinicians regarding aPDT using blue LEDs for treating halitosis on a daily basis, as most dentists already have this light source in their offices.

**Trial registration:**

ClinicalTrials.gov, NCT03346460. Registered on 17 November 2017.

**Electronic supplementary material:**

The online version of this article (10.1186/s13063-018-2913-z) contains supplementary material, which is available to authorized users.

## Background

Halitosis is an unpleasant breath odour that can interfere with the professional life, social life and quality of life of people who suffer from it [1, 2]. The prevalence of this condition may greatly vary, depending on the population. Studies show that moderate halitosis affects one third of individuals [3]. Bad breath can have both extraoral and intraoral causes, such as the use of some types of medication, dry mouth, smoking, systemic conditions and inefficient oral hygiene [1, 4]. Particularly in young patients, the presence of tongue coating seems to be the main cause of halitosis [5]. To diagnose halitosis, some tests can be conducted [6]. Among them, the organoleptic method is very often used; however, it is considered a subjective measure. The use of the Oral Chroma™, on the other hand, is the most indicative way of determining the presence of halitosis, since it has the ability to distinguish between the volatile sulphur compounds (VSCs) responsible for halitosis. Additionally, it can determine not only the presence of halitosis, but also its origin, according to the most prevalent gases [7].

The most common treatments for halitosis include the use of mouthwashes, periodontal treatment, oral hygiene instructions and tongue coating cleaning [8, 9]. While the mechanical removal of tongue coating can be easily done by patients themselves and is widely recommended, it is an oral hygiene procedure that is little practiced due to discomfort or lack of awareness [10]. Regarding mouthwashes, some of them seem to be efficient in the temporary reduction of halitosis, but few data with respect to their efficiency in tongue coating reduction are available [11–13]. The combination of more than one treatment, such as tongue cleaning associated with periodontal treatment and rinses, always seems to have better results [13, 14], which indicates the complexity of the problem. Considering this, it is thus necessary to do more research in this area, introducing new techniques for the reduction of this condition.

A modality of treatment that has been increasing in dentistry is antimicrobial photodynamic therapy (aPDT). This therapy is based on the principle that the combination of a dye, called a photosensitizer (PS), with an appropriate wavelength light source and the ambient oxygen can produce reactive oxygen species that may lead to the death of microorganisms [10]. aPDT presents a series of advantages, such as unlikely development of resistance by bacteria and the fact that it is a non-invasive procedure [15]. Its use is being studied in several areas in dentistry, such as periodontics [16] and endodontics [17] and in the treatment of mucosa wounds [18] and caries [19]. aPDT has also been used in clinical trials for the reduction of halitosis with methylene blue and red lasers, and satisfactory results have been obtained [7, 20–22].

*Bixa orellana*, popularly known as “urucum”, is a plant native to Brazil. The seeds are used to produce a dye that is largely used in the food, textile, paint and cosmetic industries. This dye is one of the few that are accepted by the World Health Organization (WHO), due to the fact that it is not toxic [23]. It has important antioxidant and antimicrobial activities [24], and recent studies have shown its potential as a therapeutic agent, source of drugs and natural dye [23, 25]. Also, the use of red/yellowish dyes, such as curcumin, is being researched for their application in aPDT [26, 27]. Due to its positive characteristics, especially regarding the lack of mutagenic and cytotoxic activity, allied to the promising results reported by laboratory studies regarding its antimicrobial effect, *Bixa orellana* extract could be considered a suitable candidate as a PS. Besides that, most dentists already have blue light-emitting diodes (LEDs) in their offices, so using a red dye with these LEDs would make aPDT treatment more accessible.

### Hypothesis

Based on this background, this research will test the hypothesis that aPDT with *Bixa orellana* extract and blue LED is effective in the reduction of halitosis.

### Objective

The aim of this study is to verify whether aPDT with *Bixa orellana* extract and blue LED is effective in the reduction of halitosis, providing an accessible treatment for this condition, as the majority of dentists already have this sort of device in their offices. This method will also be compared with tongue scraping, the most commonly used conventional method for tongue coating removal, and the association of both methods will also be evaluated.

## Methods/design

### Study design

The protocol is in accordance with the 2013 Standard Protocol Items: Recommendations for Interventional Trials (SPIRIT) Statement. The SPIRIT checklist can be found as Additional file 1, and the schedule of enrolment, interventions and assessments of the present study is depicted in Fig. 1.

**Fig. 1 Fig1:**
[figure not shown]
Schedule of enrolment, interventions and assessments of the present study

This study has been approved by the Ethics Committee of Universidade Nove de Julho under process number 74228417.2.0000.5511. Possible changes in this project shall be reported to the committee. All participants who agree to participate voluntarily will sign an informed consent form, as stipulated in Resolution 466/2012 of the Brazilian National Board of Health. A randomized clinical trial will be conducted at the dental clinic of the Universidade Nove de Julho*.* Patients will be divided by block randomization into three groups (*n* per group = 13), according to the treatment to be performed (Fig. 2). Opaque envelopes will be identified, and a sheet containing the information of the corresponding experimental group will be inserted. The envelopes will be sealed and will remain sealed in numerical order in a safe place until execution of the procedures.

**Fig. 2 Fig2:**
[figure not shown]
Trial activity flowchart

### Participants

Students and employees from the Universidade Nove de Julho will be screened, and 39 subjects who fulfil the inclusion and exclusion criteria will be selected to participate in this research.

The inclusion criteria are as follows: patients of both genders, from 18 to 25 years old, who present a volatile sulphur compounds (SH_2_) ≥ 112 ppb measured using the Oral Chroma™.

The exclusion criteria are as follows: individuals with dentofacial anomalies (such as cleft lip or cleft palate), who are undergoing orthodontic and/or orthopaedic treatment, who have periodontal diseases (such as gingivitis or periodontitis) or dental cavities, who are undergoing oncological treatment, with systemic alterations (gastrointestinal, renal, hepatic), who have undergone antibiotic therapy up to 1 month before the survey, who are pregnant or who are smokers.

### Sample composition

To calculate the sample size, the data from the article by Costa da Mota et al. [21] were used. We established an error $$ err=\left|\overline{x_1}-\overline{x_2}\right| $$, where $$ \overline{x_1} $$ and $$ \overline{x_2} $$ are the baseline values for periodontal treatment with aPDT. From this error, the effect size was calculated, given by:$$ \frac{err}{\sqrt{\sigma_1^2+{\sigma}_2^2}} $$where $$ {\sigma}_1^2 $$ and $$ {\sigma}_2^2 $$ are the variances of Groups 1 and 2, respectively.

Assuming that the studied groups have a normal or approximately normal distribution, that the sample size will be sufficiently large and that a two-tailed test will be used, for a significance level α = 0.05 and maintaining the power of the test 1 – β = 0.90 we have Group 1: 13 patients, Group 2: 13 patients, Group 3: 13 patients.

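### The sample size takes its effect from a difference between baseline values, so the stated 90% power with 13 per group is not supported for the trial's comparisons

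*Protocol article*

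**What the plan says.** The Sample composition section uses data from a cited earlier trial (reference 21). It defines err as the absolute difference between two means, which "are the baseline values for periodontal treatment with aPDT". It continues: "From this error, the effect size was calculated, given by" err divided by the square root of the sum of two variances, which "are the variances of Groups 1 and 2, respectively". It assumes approximate normality, a sufficiently large sample and "that a two-tailed test will be used". Then, "for a significance level α = 0.05" and "maintaining the power of the test 1 – β = 0.90", it arrives at 13 patients in each of three groups.

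Other sections fix what the trial tests:

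- **Hypothesis and Objective:** aPDT with *Bixa orellana* and blue LED reduces halitosis. The comparison with scraping, and the evaluation of the combination, come second.
- **Statistical analysis:** ANOVA with Tukey between the three groups and a paired t test within each treatment over time, with rank-based alternatives to both.
- **Discussion:** the results immediately after treatment are ranked as the most important.
- **Participants:** people are excluded "who have periodontal diseases (such as gingivitis or periodontitis) or dental cavities", and under Interventions no arm receives periodontal treatment.

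**The concern.** Baseline values are measured before anything has been done to the patient, so a difference between two of them says nothing about what a treatment achieves. A power figure needs a difference that some planned test is meant to detect, and the one described is not of that kind.

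The 90% figure is the only statement of how informative 39 patients will be. If it stands, a non-significant comparison between scraping, aPDT and the combination could be read as good evidence that they perform alike. In fact only differences well above 1 SD would be detected reliably between arms.

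**Working it through.** **Inputs from Sample composition.** Two-sided α = 0.05, power 0.90, 13 per group, and effect size es = err/√(σ₁² + σ₂²). The article prints no means or variances, so 13 cannot be derived forwards. It can be solved backwards.

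**Step 1. Effect implied by 13 per group (normal approximation, two means).**
n = (z₀.₉₇₅ + z₀.₉₀)² / es², with 1.960 + 1.282 = 3.242.
- n = 13.0: es = 3.242/√13 = 0.899
- n = 12.0: es = 3.242/√12 = 0.936

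Any es from 0.899 up to just under 0.936 rounds up to 13. With equal variances, the difference in SD units is d = es × √2, which is 1.27 to 1.32 SD.

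**Step 2. Literal reading: a difference between baselines.** This is not an effect of any treatment. No between-arm or within-arm contrast in the Statistical analysis section corresponds to it, so the 90% attaches to none of them.

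**Step 3. If a before-after change was meant.** The SD of a paired difference is √(σ₁² + σ₂² − 2rσ₁σ₂). With equal variances the paired effect is es/√(1 − r). The correlation r is not given and is assumed here. Taking es = 0.899, n = 13 and a paired t test with 12 df:

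| r (assumed) | paired effect | power |
|---|---|---|
| 0 | 0.899 | 84% |
| 0.16 | 0.981 | 90% |
| 0.3 | 1.075 | 94% |

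On this reading the figure is roughly right for the within-group test. It says nothing about differences between arms.

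**Step 4. If a between-arm difference was meant.** The noncentrality is d × √(13/2).
- Single two-sided 5% t test, 24 df: 87% power at 1.27 SD and 90% at 1.326 SD.
- Tukey-adjusted pair, 36 df, critical t 2.444: 78% at 1.27 SD and 82% at 1.32 SD. 90% is reached at 1.475 SD.
- For scale, at an assumed difference of 1.0 SD: 69% for the single contrast and 55% for the Tukey pair.

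**Step 5. Detectable at 90% power with 13 per group.**
- Paired test: 0.98 SD of the differences
- Single between-arm contrast: 1.33 SD
- Tukey-adjusted pair: 1.48 SD

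**The case against.** The best defence is that the word baseline is a slip for baseline versus post-treatment values. The sentence names one treatment, not two arms, which fits a before-after change. Such a change would match the Hypothesis section and the planned paired test, and treating the two measurements as uncorrelated errs on the safe side when they are positively correlated. This stands. A reader might infer that the power refers to nothing the trial tests on any reading, and the documents do not support that. The slip cannot be confirmed without the cited article, however, and the between-arm comparisons would still have no power statement.

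A reader might also infer that the source was an unrelated periodontal study with the wrong dye and light. The article does not bear this out. It cites the source among halitosis trials: "aPDT has also been used in clinical trials for the reduction of halitosis with methylene blue and red lasers". The Discussion says that aPDT studies to date used that combination, so borrowing the nearest data is ordinary planning. What remains is that the values are tied to periodontal treatment, which no arm here receives.

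Finally, the absence of printed means and SDs is not itself an error, since a condensed article may leave them to the full protocol.

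**Conclusion.** The point holds. The effect size is defined on baseline values, and the 90% power with 13 per group is therefore not supported for the trial's comparisons. On the most favourable reading, the figure is about right for the within-group test (84 to 94% for assumed correlations of 0 to 0.3) and silent on the comparison of the three groups. On a between-arm reading, the planned Tukey comparison would have about 78 to 82%, not 90%.

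These figures rest on normal data, equal variances, complete follow-up of 13 per arm, and an effect solved backwards from the stated sample size by the normal approximation.

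A reader might conclude that the trial is underpowered or that 13 is a miscalculation. Neither is shown. The article gives no target difference against which 13 could be judged too few, and the 1.0 SD case above is only an illustration.

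**What to change.** In Sample composition, replace the baseline-based err by a treatment difference in the halimetry outcome (volatile sulphur compounds) immediately after treatment. Name the contrast and its SD, and say which groups the two variances belong to. Restate power separately for the within-group paired test and for the between-group ANOVA/Tukey comparison.

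If 13 per arm is kept, withdraw the 90% claim as derived and report the three detectable differences from Step 5 of the working in its place.

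The change is to wording only and adds no patients. The Trial status section says recruitment has not begun, so it can be made in time. The cost is that the stated power becomes less favourable.

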### Statistical analysis

Data from Oral Chorma™ will be analysed for their normality by the Shapiro-Wilk test. If the normality hypothesis is accepted, the analysis of variance (ANOVA) followed by the Tukey test will be used when necessary to perform the between-groups analysis. To analyse the results of the treatment in both periods of the study, the *t* test for paired data will be used. If the normality hypothesis is rejected, the Kruskal-Wallis test followed by the Student-Newman-Keuls test, when necessary, will be used. To analyse the results of each treatment in both periods of the study, the Wilcoxon test will be used.

The kappa test will also be used to check interrater reliability in the evaluation of the presence of tongue coating.

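### The stated 90% power is for one unadjusted two-group test, but the planned between-group analysis is a three-arm ANOVA with Tukey; a Tukey pair has about 78–82% at the difference that 13 per group implies

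*Protocol article*

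**What the plan says.** The protocol article, under Sample composition, takes its planning data from a cited earlier trial. It forms the absolute difference of two means and divides it by the square root of the sum of two variances; these "are the variances of Groups 1 and 2, respectively". It assumes approximate normality, "that the sample size will be sufficiently large and that a two-tailed test will be used". It then works "for a significance level α = 0.05" and "maintaining the power of the test 1 – β = 0.90", and arrives at 13 patients in each of Groups 1, 2 and 3. The means, the SDs and the resulting effect size are not printed.

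Under Statistical analysis, for normally distributed Oral Chroma data, "the analysis of variance (ANOVA) followed by the Tukey test will be used when necessary to perform the between-groups analysis". If normality is rejected, Kruskal-Wallis followed by Student-Newman-Keuls takes its place. Paired tests within each group are also planned.

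The Objective section wants aPDT compared with tongue scraping and the combination evaluated as well. The Discussion says that the trial will compare aPDT alone with scraping alone and with the combination, to find the most efficient treatment.

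**The concern.** The power statement and the between-group test are both in this document, and they describe different tests. The first is one comparison of two groups at an unadjusted 5% level, with a large-sample approximation. The second is a three-arm test followed by pairwise comparisons that share a 5% familywise error rate. A Tukey pair has to pass a stricter threshold, so at a given difference it has less power than the single test.

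The practical risk is in reading a negative result. A reader who trusts the 90% would give a non-significant pair a 10% chance of having missed the planned-for difference. Under the assumptions below, that chance is nearer 18–22%. A non-significant pair could then be over-read as two treatments performing alike.

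**Working it through.** **Inputs from the protocol.** Two-sided alpha 0.05, power 0.90, 13 per group in three groups, effect-size ratio ES = |x1 − x2| / √(s1² + s2²) (Sample composition); ANOVA then Tukey (Statistical analysis).

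**Input not given.** The effect size. I solve for it and treat it as an assumption. With a common SD, d = |x1 − x2| / SD = ES × √2.

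**1. The plan's own figure.** The printed ratio fits the usual normal-approximation formula for two groups, n = (1.960 + 1.282)² / ES². Setting n = 13 gives ES = 3.242 / √13 = 0.899, so d = 1.271. If n was just above 12 and rounded up, d is at most 1.323. An exact t calculation (24 df) that gives 90% at n = 13 needs d = 1.326; rounding up from just above 12 allows d up to 1.385. The figure of 13 is therefore consistent with a two-group calculation, but cannot be reproduced independently because its input is not printed.

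**2. Power at 13 per arm.** The noncentrality for a pair is d × √(13/2). The two-sample t test has 24 df. With the three-arm pooled variance the error df are 3 × 12 = 36. The Tukey critical value is 3.457 / √2 = 2.444, which is a per-comparison alpha of about 0.0195.

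| Assumed d | Two-sample t, 5%, 24 df | One contrast, 5%, 36 df | One Tukey pair, 36 df |
|---|---|---|---|
| 1.271 (normal formula, n = 13) | 87.5% | 88.4% | 78.3% |
| 1.326 (exact t, n = 13) | 90.0% | 90.8% | 82.0% |
| 1.385 (exact t, rounded up from 12) | 92.3% | 93.0% | 85.6% |

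If a significant F is required before the Tukey pair counts, the first two rows give 77.2–81.7% (simulation, 200,000 runs per setting).

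**3. Splitting the gap.** At d = 1.271 the total shortfall is 90 − 78.3 = 11.7 points. Of this, 90 − 87.5 = 2.5 points come from using the normal approximation at 13 per group, which a plain t test would lose too. At d = 1.326 that part is absent and the loss is 90.0 − 82.0 = 8.0 points.

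**4. Omnibus F (2 and 36 df).** With the third mean midway, the noncentrality is 13d²/2 and power is 80.1% at d = 1.271 and 83.5% at d = 1.326. With the third mean equal to one of the others, it is 2 × 13d²/3 and power is 90.5% and 92.8%.

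**5. What 90% per Tukey pair would take.** 18 per arm at d = 1.271 or 16 per arm at d = 1.326; or, with 13 per arm, a difference of about 1.48 SD.

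The Kruskal-Wallis/Student-Newman-Keuls branch and the paired within-group tests were not assessed.

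**The case against.** The strongest reply is that no mean, SD or effect size is printed, so every percentage above rests on a back-solved difference. That stands. The direction of the loss is general, because Tukey always asks more than a single 5% test. Its size is conditional. A reader might infer that the design lacks 90% whatever effect was used, and the document does not support that. If the printed ratio was entered in software as Cohen's d, the true d would be about 1.80–1.87, Tukey power about 98–99%, and the shortfall would vanish. The document does not say that this was done.

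Second, it is tempting to attach 78–82% to the ANOVA as a whole. That is wrong. It is the power of one specified Tukey pair; the omnibus F exceeds 90% when the third mean equals one of the others. But a significant F alone does not say which treatment is best, and that is the comparison the Discussion wants.

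Third, the whole gap should not be put down to three arms: about 2.5 points at the lower end come from the normal approximation. Nor may the same loss be read across to the non-normal branch, since Student-Newman-Keuls is stepwise and less conservative than Tukey.

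What survives is the mismatch itself. The stated power is for a test that the plan does not use between groups.

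**Conclusion.** The point holds as a mismatch between the sample-size basis and the planned analysis. It is not an arithmetic error: no printed figure is shown to be miscalculated, and none can be checked. Assuming normal data with equal variances and a difference of 1.27–1.33 SD, 13 per arm gives one Tukey-adjusted pair about 78–82% power, and about 86% at the most favourable rounding (1.385 SD), against a stated 90%. Confidence is high that the 90% describes a different test, and only moderate on the size, because the planning effect is not shown. The matter should be corrected; it does not invalidate the design.

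**What to change.** Under Sample composition, print the assumed difference and SD, say how they were entered in the calculation, and then take one of two routes.

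- **Restate the power for the test actually used.** At 1.3 SD this is about 80% per Tukey-adjusted pair with 13 per arm. If the printed inputs imply another difference, recompute.
- **Pre-name one primary between-group contrast.** Test it at two-sided 5% with the three-arm pooled variance, which gives about 88–91% power at 1.27–1.33 SD, and make the other two pairs secondary. The choice of contrast is the sponsor's. The Objective, which names aPDT against scraping first, and the sample-size formula, which uses the variances of Groups 1 and 2, both point to Group 2 versus Group 1.

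The cost is a slightly lower stated power on the first route, or two pairs demoted to secondary on the second. Neither adds patients, and the article states that recruitment has not begun, so the change can be made before any data exist.
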